#### Inclusion criteria

Women aged 15–35 years with at least one (index) child aged 2–4 years living in the same household in the targeted villagesChildren aged 0–5 years at baseline whose mothers and index sibling are included in the studyHouseholds of women included in the study

#### Exclusion criteria

Household head, child, parent, or guardian unwilling to participate in the studyHouseholds planning to move out of the study area within six months after the baseline surveyHouseholds were located in villages that were too small to have 15 or more households with children in the 2–4-year age group based on latest DHS demographics or too large to be considered rural (with population over 5000 people (or over 95% of the population distribution)

### Random assignment and manipulation of treatments

Communities will be randomly assigned to one of three treatment arms:SELEVER intervention group: communities where the SELEVER program is implemented;SELEVER+: communities where the SELEVER program is implemented alongside an intensive WASH component;Control group: communities with no intervention, for at least the four years of the study duration.

The SELEVER intervention is implemented at the commune level as the training, sensitization, and BCC involve commune level stakeholders. During the preparation stage, 60 communes were selected from a pool of 79 communes that were available for scale-up by SELEVER in the targeted regions. The criteria for commune selection included: (1) not included in the SELEVER pilot communes; (2) classified as rural or peri-urban (as classified in the national census); (3) year-round accessibility by road; and (4) for the Hauts-Bassin region communes, proximity to the Boucle de Mouhoun and Centre Ouest regions. The first stage of randomization was aimed at randomizing the 60 communes in the study into two groups (SELEVER and control) and provides the basis for the main trial comparisons (SELEVER – Control). Due to the relatively small number of clusters in the study, to ensure balance in the comparison groups the random allocation was undertaken through restricted randomization by modeling selection using a set of commune-level and village-level variables obtained through the national census of 2006.

Following Hayes and Moulton [16], the variables in the restricted randomization were selected on availability and their potential influence on the main study outcomes. The variables in the model included population size, existence of a government center, number of female associations, main agricultural crop, main source of revenue, market presence, health center presence, number of functional boreholes, and number of functional wells. Village level data were also used to generate commune level aggregates for population size, number of health centers, number of boreholes, and market access. Villages that were too small to allow for a subsequent survey sample to be drawn (likely to have less than 15 households with children in the 2–4-year age group based on latest DHS demographics) or too large to be considered rural (with a population of over 5000 people or over 95% of the population distribution) were excluded from the list. A program was developed using Stata to randomly allocate communes to two different groups stratifying by region and then select two villages in each commune from the list of available villages. The algorithm then regressed the selection into the treatment group based on the village-level and commune-level covariates. The routine tested 3000 random allocations and selected the permutation that minimized the r^2^ statistic for the predicted selection. The second stage of randomization will provide the basis for the WASH sub-study comparisons (SELEVER+/SELEVER – Control). The 30 SELEVER village pairs (one pair for each commune) will be randomly assigned to either the SELEVER intervention or SELEVER+, and 15 communes from the control group will also be selected for the sub-study using a similar restricted randomization procedure (Fig. 1 and 2).

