### Sample sizes

Power calculations (Table 2) and resource availability suggested the adoption of a dual sampling strategy: For the outcomes in the main trial comparison (SELEVER vs. control), 15 households from each of the 120 villages in the study will be surveyed at baseline and end line surveys, for a total of 1800 households. A sub-sample of 1080 households, women and children dyads (or pairs) will be included for detailed and more frequent assessments (see “Data collection and outcome measurement”).

**Table 2 Tab2:** Minimum detectable effect size estimates and summary of parameters used in sample size calculations for the main study outcomes^a^

	Women’s dietary MPA	Children’s dietary MPA (3–5 years)	Children DD (6–24 months) (n. of food groups)	Household poultry production	Household poultry sales
Communes (n per intervention arm)	15	15	30	30	30
Villages (n per intervention arm)	30	30	60	60	60
Individuals per village (n)	12	12	8.8	15	15
Intra-cluster correlation (level 3)	0.002	0.002	0.001	0.001	0.001
Intra-cluster correlation (level 2)	0.05	0.04	0.05	0.06	0.01
Sample size (per intervention arm)	360	360	526	900	900
Estimated baseline levels	0.26	0.43	3.95	11	1
Standard deviation (baseline)	0.22	0.31	0.97	11	3
Minimum detectable effect size (SD)	0.28	0.27	0.21	0.18	0.15
Minimum detectable effect size (eq. levels)	0.06	0.08	0.20	1.98	0.45

^a^Estimates based on type I error of 5% (two-sided test) and statistical power of 80%

*MPA* mean probability of adequacy, *DD* dietary diversity

During the baseline survey, a household census will be conducted to identify all the large poultry producers in the community, households with women in the target groups (women aged 15–35 years with children in the target age group), and collect other basic household level information necessary for the sample selection. Households will then be randomly selected from the household census for the survey interviews. Large poultry-producing households (e.g. defined as owning a poultry flock of over 20 chickens/fowls) will be oversampled (6/15 households will be large poultry-producing households). This distribution of the sample will enable the construction of comparable samples for the main trial comparisons, also allowing for analysis of direct and indirect effects by including both beneficiary and non-beneficiary households in the survey population.

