For the power calculations, we used data from an observational study examining food intake in two of the three regions of interest (Centre-Ouest and Boucle du Mouhoun) [17, 18] and from the impact evaluation of the Hellen Keller International homestead food production intervention in Burkina Faso [19]. The power calculations for the primary outcomes for women, children, and households are based on 80% statistical power and alpha value of 0.05 (Table 2). With a random sub-sample of 360 women and children per treatment arm in the detailed biomedical assessment, we can estimate effect sizes for the primary outcomes of about 0.28 z-scores in the MPA for women and children. This effect size is equivalent to about 6 points in MPA, which is approximately half the absolute difference observed between MPAs in the post-harvest and lean seasons in the targeted regions of Burkina Faso [17]. Considering that dietary assessment is quite time-consuming in terms of both data collection and analysis, and that biomarker status assessment is invasive and quite expensive, it is appropriate to limit assessment of these indicators to the required sub-sample only. The individual PA for a specific nutrient is compiled using the probability approach to compare the usual nutrient intake to the relevant population requirement distribution [20]. Therefore, its average at the population level can be interpreted as the prevalence of adequacy of intake for this specific nutrient. The MPA is an aggregate measure of the adequacy of intake across a range of key nutrients, in this case iron, zinc, and vitamin A. The other primary outcomes (e.g. dietary diversity, household poultry production, and sales) will require a larger sample size to detect a meaningful impact. With the full sample based on 900 households per treatment arm in the main trial (SELEVER – Control), we can detect effect sizes ranging from 0.18 z-scores (e.g. household poultry production) to 0.15 z-scores (e.g. household poultry sales). Power estimates for the study’s end line survey will be reassessed based on actual levels and intracluster correlations in our survey and estimated typical level of attrition based on similar study designs (set at 5%).

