**Fig. 3 Fig3:**
[figure not shown]
Stylized high-level data collection timeline

**Table 3 Tab3:** Measurement schedule for key study indicators

*Main trial comparisons*			Survey round				
Longitudinal, 1800 households			BL (Feb 2017)	R2 (Aug 2017)	R3 (Aug 2019)	R4 (Feb 2020)	R5 (Feb 2021)
Primary	Dietary intake	Dietary diversity (women and children)	I			I	I
	IYCF practices	Minimum acceptable diet (6–24 months)	I			I	I
	Poultry output	Production, sales, and profits	I			I	I
Secondary	Women’s empowerment	WEAI	I			I	I
	Maternal stress and wellbeing		I			I	I
	Poultry VC		I			I	I
	Morbidity	Recall of diarrhea, fever, and chest infections	I			I	I
	Hygiene	Exposure to poultry feces and cleanliness	O			O	O
		Hygiene knowledge	I			I	I
	Women’s nutrition knowledge	Nutrition KAP	I			I	I
	Nutrition	Anthropometry	M			M	M
	Expenditures		I			I	I
	Other household and maternal factors		I			I	I
*WASH sub-study comparisons*			Survey round				
Longitudinal, 1080 households			BL (Feb 2017)	R2 (Aug 2017)	R3 (Aug 2019)	R4 (Feb 2020)	R5 (Feb 2021)
Primary	Dietary intake	Probability of adequacy (Fe, Zn, Vit A), IDDS	I	I	I	I	I
	IYCF practices	Minimum acceptable diet (6–24 months)	I	I	I	I	I
	Poultry output	Production, sales, and profits	I	I	I	I	I
Secondary	Maternal stress and wellbeing		I	I	I	I	I
	Poultry VC		I	I	I	I	I
	Morbidity	Recall of diarrhea, fever, and chest infections	I	I	I	I	I
	Hygiene	Exposure to poultry feces and cleanliness	O	O	O	O	O
		Hygiene knowledge	I	I	I	I	I
	Women’s nutrition knowledge	Nutrition KAP	I	I	I	I	I
	Nutrition	Anthropometry	M	M	M	M	M
	Expenditures		I	I	I	I	I
	Other household and maternal factors		I	I	I	I	I
	Micronutrient status (children)	Hemoglobin (Hb)	B			B	B
		Plasma ferritin (PF)	B			B	B
		Soluble transferrin receptor (sTfR)	B			B	B
		Retinol-binding protein (RBP)	B			B	B
	Infection (children)	Serum C-reactive protein (CRP)	B			B	B
		α-1-acid glycoprotein (AGP)	B			B	B
		Malaria	B			B	B
		Pathogenic gut bacteria	S			S	S
	Cognition (children)		T			T	T

*B* blood, *BL* baseline, *I* interview, *IDDS* individual dietary diversity score, *IYCF* infant and young child feeding, *KAP* knowledge attitude practices, *M* measurement, *O* observation, *R* follow-up round, *S* stool, *T* test, *WEAI* Women’s Empowerment in Agriculture Index

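### In the full-sample SELEVER v control comparison, 80% of intervention but 40% of control households are intensively measured, so the pooled estimate carries 0.40 times any effect of measurement, of unknown size and sign

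*Protocol article*

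**What the plan says.** Under Random assignment and manipulation of treatments, the protocol describes two stages. "The first stage of randomization was aimed at randomizing the 60 communes in the study into two groups (SELEVER and control"), which gives 30 communes per side. Then "The 30 SELEVER village pairs (one pair for each commune) will be randomly assigned to either the SELEVER intervention or SELEVER" with the added WASH component, so every intervention commune takes part in the WASH sub-study comparisons. For the control side, "15 communes from the control group will also be selected for the sub-study using a similar restricted randomization procedure".

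Under Sample sizes, the survey size is set: "15 households from each of the 120 villages in the study will be surveyed at baseline and end line surveys, for a total of 1800". Of these, a part is followed more closely: "A sub-sample of 1080 households, women and children dyads (or pairs) will be included for detailed and more frequent assessments". Table 2 puts the sub-study at 15 communes, 30 villages and 12 individuals per village in each of three arms.

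Table 3 lists the main-trial panel at baseline, R4 and R5. The sub-study panel ("Longitudinal, 1080 households") is seen at baseline, R2, R3, R4 and R5. The sub-study also has the dietary recalls, blood and stool samples and child cognition tests.

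The main comparison is powered on all 1800 households, 900 on each side. On that basis the protocol states what it can find: "we can detect effect sizes ranging from 0.18 z-scores (e.g. household poultry production) to 0.15 z-scores (e.g. household poultry sales"). The Methods of analysis section names a difference-in-difference and an ANCOVA estimator, mixed models with commune, village and household random effects, and a robustness check on the balancing variables. It mentions no role for sub-study membership.

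**The concern.** Measurement intensity is tied to arm by the design itself. R2 and R3 come before the R4 end line and ask about feeding practices, dietary diversity, poultry production, sales and profits, and nutrition and hygiene knowledge. Several of these are the primary outcomes that the full sample is later compared on, and the programme's own behavior change messages cover the same subjects. The outcomes are interview-reported. Repeated detailed questioning might change what households do or how they answer.

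If it does, randomisation does not cancel the effect, because the share of heavily measured households differs between the arms. Baseline adjustment does not cancel it either, because the extra rounds come after baseline. At stake is the reading of the full-sample results for dietary diversity, minimum acceptable diet and poultry output.

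**Working it through.** **1. Reproduce the plan's counts.** Inputs are from the randomisation section, Sample sizes and Table 2.
- Sub-study: 15 communes × 2 villages × 12 = 360 per arm; × 3 arms = 1080. This matches.
- Full sample: 120 × 15 = 1800; 60 villages × 15 = 900 per main-trial arm. This matches.

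**2. Share intensively measured in the 900 v 900 comparison.**
- Intervention (SELEVER and SELEVER+ pooled): 2 × 360 / 900 = 80%.
- Control: 360 / 900 = 40%.
- Mean rounds per household: 3 + 2 × 0.80 = 4.6 v 3 + 2 × 0.40 = 3.8.

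**3. Bias.** If intensive measurement shifts an outcome by δ (in SD), the unadjusted arm difference contains (0.80 − 0.40) × δ = 0.40δ. A generalised least squares calculation with 60 communes, 2 villages, 15 households per village and Table 2's intra-cluster correlations returns a coefficient of exactly 0.40. For child outcomes the shares assume that eligible children are spread evenly over sub-study and other households.

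**4. Type I error.** SE = MDE / (1.960 + 0.842) = MDE / 2.802, where MDE is the minimum detectable effect in Table 2. The rejection rate under no programme effect is P(|Z + 0.40δ/SE| > 1.96). It is the same for +δ and −δ. The documents give no δ, so the values below are assumptions.

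| Assumed size of δ (SD) | Bias (SD) | Sales, MDE 0.15 | Production, MDE 0.18 | Child dietary diversity, MDE 0.21 |
|---|---|---|---|---|
| 0 | 0 | 5% | 5% | 5% |
| 0.05 | 0.02 | 6.6% | 6.1% | 5.8% |
| 0.10 | 0.04 | 11.6% | 9.5% | 8.3% |
| 0.20 | 0.08 | 32.1% | 23.8% | 18.7% |

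If δ is negative, a real programme effect is understated. For sales at its MDE, δ = −0.10 SD gives a shift of 0.04/0.0535 = 0.747 standard errors. Power falls from 80% to about Φ(2.802 − 0.747 − 1.960) = Φ(0.095) ≈ 54%.

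**5. Cost of adding a household-level sub-study indicator** (same least squares set-up). The SE of the programme effect is multiplied by 1.06 for production (MDE 0.181 to 0.192 SD), 1.09 for sales (0.143 to 0.155 SD) and 1.06 for dietary diversity (taken at 15 per village for simplicity).

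**6. Precision of the possible checks.** For comparisons with equal numbers per village within an arm, MDE = 2.802 × √[sum over arms of (ICC3/communes + ICC2/villages + (1 − ICC2 − ICC3)/households)].
- Sub-study households only, 720 v 360, production: 0.001/30 + 0.06/60 + 0.939/720 + 0.001/15 + 0.06/30 + 0.939/360 = 0.00701; MDE = 2.802 × 0.0837 = 0.23 SD. Sales, with ICC2 = 0.01: 0.19 SD.
- Households outside the sub-study: 60 × 3 = 180 intervention v 30 × 3 + 30 × 15 = 540 control. By least squares the MDE is about 0.27 SD (production) and 0.25 SD (sales).
- The 15 sub-study v 15 other control communes: the contrast is diluted to 0.80δ because 12 of 15 households are measured. Power is about 14% (production) and 20% (sales) at δ = 0.1 SD, and 42% and 60% at 0.2 SD.

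**The case against.** The counts are not in dispute; the consequence is.

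- **Size and sign are unknown.** A reader might infer from the imbalance that the design inflates the programme effect. The documents do not support this. Fatigue, or less over-reporting after repeated recalls, would push the other way; at 0.05 SD the error rate hardly moves, and at zero there is no bias. This stands: the imbalance is certain, the harm is not.
- **An equally measured comparison is already in the data.** Table 3 lists dietary diversity, minimum acceptable diet and poultry output as primary in the sub-study too, at R4 and R5. This stands and supplies the best check, at some loss of precision (0.23 v 0.18 SD for production).
- **The extra exposure is limited.** Spot checks and knowledge interviews reach all 1800 households at baseline, R4 and R5. R2 precedes R4 by 30 months, R3 by six. Children aged 6–24 months at R4 were not born at R2, so an effect of that round must pass through the caregiver. This argues for a small effect but does not establish one.
- **The dual sample is deliberate.** The protocol justifies it by resources, the time that dietary assessment takes, and the invasiveness and cost of biomarkers. That explains a sub-sample, but the pooled 900 v 900 comparison still mixes unequal shares.
- **Model terms belong in an analysis plan.** Nothing in the article excludes an indicator, and its absence alone would be no finding. The point rests on the allocation and the pooled comparison, both of which the article fixes.

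**Conclusion.** The point holds in a limited form. The full-sample estimates at R4 and R5 contain 0.40 times any measurement effect. For assumed effects of 0 to 0.2 SD in either direction, the bias is 0 to 0.08 SD, against stated detectable effects of 0.15 to 0.21 SD. The nominal 5% test then rejects a true null between 5% of the time and, at the upper end, 19–32%.

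The 80% and 40% shares follow exactly from the protocol. The size of the bias rests wholly on the assumed δ. It should not be read as showing that SELEVER's effect will be overstated, since the bias could equally hide a real effect. The micronutrient adequacy outcomes (PA and MPA) and the biomarkers are compared at 360 per arm among equally measured households and are not affected.

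Because the exposed outcomes include several that Table 3 calls primary and the repair needs no new data, it should be made.

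**What to change.** For the full-sample outcomes at R4 and R5:

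1. Add a household-level indicator of sub-study membership to the main model, or at least report that model as a pre-specified sensitivity analysis beside the unadjusted estimate. The indicator is usable as a covariate because membership is set by random selection of households and, in control, by restricted random selection of communes.
2. Report the comparison within sub-study households (720 v 360) as the main check, since measurement there is the same in all arms.
3. Give the contrast of sub-study with other control communes, and the analysis of households outside the sub-study (180 v 540), only as low-power supporting checks. A null result in either should not be taken as reassurance.
4. State the limits: a single term assumes the same measurement effect in both arms, and it cannot remove spillover within villages, because every intervention village contains sub-study households.

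The cost is one model term and a few short tables, with no new data. The standard error of the adjusted programme effect widens by about 6–9%.

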**Fig. 1 Fig1:**
[figure not shown]
*Schematic view* of the randomization

**Fig. 2 Fig2:**
[figure not shown]
Map of study communes and first stage randomization

### Sample sizes

Power calculations (Table 2) and resource availability suggested the adoption of a dual sampling strategy: For the outcomes in the main trial comparison (SELEVER vs. control), 15 households from each of the 120 villages in the study will be surveyed at baseline and end line surveys, for a total of 1800 households. A sub-sample of 1080 households, women and children dyads (or pairs) will be included for detailed and more frequent assessments (see “Data collection and outcome measurement”).

**Table 2 Tab2:** Minimum detectable effect size estimates and summary of parameters used in sample size calculations for the main study outcomes^a^

	Women’s dietary MPA	Children’s dietary MPA (3–5 years)	Children DD (6–24 months) (n. of food groups)	Household poultry production	Household poultry sales
Communes (n per intervention arm)	15	15	30	30	30
Villages (n per intervention arm)	30	30	60	60	60
Individuals per village (n)	12	12	8.8	15	15
Intra-cluster correlation (level 3)	0.002	0.002	0.001	0.001	0.001
Intra-cluster correlation (level 2)	0.05	0.04	0.05	0.06	0.01
Sample size (per intervention arm)	360	360	526	900	900
Estimated baseline levels	0.26	0.43	3.95	11	1
Standard deviation (baseline)	0.22	0.31	0.97	11	3
Minimum detectable effect size (SD)	0.28	0.27	0.21	0.18	0.15
Minimum detectable effect size (eq. levels)	0.06	0.08	0.20	1.98	0.45

^a^Estimates based on type I error of 5% (two-sided test) and statistical power of 80%

*MPA* mean probability of adequacy, *DD* dietary diversity

During the baseline survey, a household census will be conducted to identify all the large poultry producers in the community, households with women in the target groups (women aged 15–35 years with children in the target age group), and collect other basic household level information necessary for the sample selection. Households will then be randomly selected from the household census for the survey interviews. Large poultry-producing households (e.g. defined as owning a poultry flock of over 20 chickens/fowls) will be oversampled (6/15 households will be large poultry-producing households). This distribution of the sample will enable the construction of comparable samples for the main trial comparisons, also allowing for analysis of direct and indirect effects by including both beneficiary and non-beneficiary households in the survey population.

For the power calculations, we used data from an observational study examining food intake in two of the three regions of interest (Centre-Ouest and Boucle du Mouhoun) [17, 18] and from the impact evaluation of the Hellen Keller International homestead food production intervention in Burkina Faso [19]. The power calculations for the primary outcomes for women, children, and households are based on 80% statistical power and alpha value of 0.05 (Table 2). With a random sub-sample of 360 women and children per treatment arm in the detailed biomedical assessment, we can estimate effect sizes for the primary outcomes of about 0.28 z-scores in the MPA for women and children. This effect size is equivalent to about 6 points in MPA, which is approximately half the absolute difference observed between MPAs in the post-harvest and lean seasons in the targeted regions of Burkina Faso [17]. Considering that dietary assessment is quite time-consuming in terms of both data collection and analysis, and that biomarker status assessment is invasive and quite expensive, it is appropriate to limit assessment of these indicators to the required sub-sample only. The individual PA for a specific nutrient is compiled using the probability approach to compare the usual nutrient intake to the relevant population requirement distribution [20]. Therefore, its average at the population level can be interpreted as the prevalence of adequacy of intake for this specific nutrient. The MPA is an aggregate measure of the adequacy of intake across a range of key nutrients, in this case iron, zinc, and vitamin A. The other primary outcomes (e.g. dietary diversity, household poultry production, and sales) will require a larger sample size to detect a meaningful impact. With the full sample based on 900 households per treatment arm in the main trial (SELEVER – Control), we can detect effect sizes ranging from 0.18 z-scores (e.g. household poultry production) to 0.15 z-scores (e.g. household poultry sales). Power estimates for the study’s end line survey will be reassessed based on actual levels and intracluster correlations in our survey and estimated typical level of attrition based on similar study designs (set at 5%).

